***Confidential***

# Abbreviations

| AF | Atrial fibrillation |
| --- | --- |
| LAA | Left atrial appendage |
| TEE | Trans-esophageal echocardiography |

| **Title of Study** | **Fusion imaging during left atrial appendage closure** |
| --- | --- |
| **Principal Investigator** | PD [name] |
| **Sub-Investigators** | [name]  [name]  [name]  [name] |
| **Study Duration** | First patient in: Q1 2012  Recruitment Phase: 24 months Observational period per patient: 3-12 months  Last patient out: Q4 2014 |
| **Legal Aspects** | The study will be performed in accordance with the Declaration of Helsinki and the Good clinical practice (GCP)-guideline. |
| **Background** | Percutaneous left atrial appendage (LAA) closure is currently under investigation as a promising catheter-based approach for stroke prevention in patients with atrial fibrillation (AF) [1,2,3]. This is important since the LAA is the source of thrombi in >90% of affected patients with nonvalvular AF [4] while oral anticoagulation still bears several limitations including bleeding risk [2]. Importantly, LAA closure still remains technically challenging and exposes patients to a considerable risk [5]. Recently, a novel system enabling integrated echocardiography and fluoroscopy imaging (EchoNavigator®), Philips Healthcare), has been introduced [6,7]. The usefulness of this novel imaging approach during LAA closure procedures has not been investigated so far. Herein, we investigate the utility of LAA closure guided by integrated echocardiography and fluoroscopy imaging. |
| **Risk-Benefit-Assessment** | All patients with nonvalvular AF, a CHA2DS2-VASc score of ≥1 and a relative contraindication to oral anticoagulation will be assigned to LAA closure for stroke prevention. LAA closure still remains technically challenging and exposes patients to a considerable risk [5]. The EchoNavigator® system might at least partly overcome these limitations including radiation exposure [6,7]. Only patients with a medical indication for LAA closure will be included in this observational study. Standard procedures using CE certified techniques will be used, no additional risk is expected. The presented observational study is part of a study protocol aiming to characterize circulatory parameters to prevent hemodynamic instability (Clinical Trial Registration: URL: http://clinicaltrials.gov. Unique Identifier: NCT01262508). |
| **Objectives** | To investigate whether percutaneous left atrial appendage (LAA) closure guided by the EchoNavigator® system results in decreased radiation exposure.  **Primary outcome:** Primary endpoints are the change of total radiation dose and fluoroscopy time.  **Secondary outcomes:** Secondary endpoints are the change of procedure time and contrast media amount. Successful LAA closure (residual flow <5mm) and acute (7-day) occurrence of death, ischemic stroke, systemic embolism and procedure or device related complications requiring major cardiovascular or endovascular intervention are determined |
| **Study Design** | non-interventional, open-label, single-center, observational study |
| **Inclusion Criteria** | - Male and female patients aged > 18 years - Patients with nonvalvular AF, a CHA2DS2-VASc score of ≥1, a relative contraindication to oral anticoagulation, and a life expectancy of at least 2 years - Group 1: LAA closure with the guidance of automated real-time integration of 2D-/3D-trans-esophageal echocardiography (TEE) and fluoroscopy imaging (EchoNavigator®) - Group 2: LAA closure without the guidance of automated real-time integration of 2D-/3D-TEE and fluoroscopy imaging (EchoNavigator®) - Written informed consent |
| **Exclusion Criteria** | - Patients unwilling or unable to give informed consent - Underage persons |
| **Number of Patients** | All patients with nonvalvular AF, a CHA2DS2-VASc score of ≥1 and a relative contraindication to oral anticoagulation who will undergo a LAA closure procedure at the Heart Center Duesseldorf will be asked to participate in this observational study. The recruitment period will be 24 months. |
| **Intervention** | All included patients with nonvalvular AF, a CHA2DS2-VASc score of ≥1 and a relative contraindication to oral anticoagulation will undergo LAA closure with or without the Echo-navigator® System at the Heart Center Duesseldorf according to local standard. The procedure will be performed either in deep sedation using TEE and fluoroscopy for guidance. |
| **Methods** | After patients given their written informed consent the following data will be collected:   - Demographics and medical history - Physical examination and vital signs - Periprocedural in hospital data, e.g. procedure duration and radiation time - Laboratory parameters (blood samples for biochemistry and hematology analysis) - Trans-thoracic echocardiography - TEE   Follow-up visits will be performed routinely after 3, 6, and 12 months. The following outcome parameters will be collected:   - Physical examination and vital signs - Medical history |
| **Data Documentation** | All data to be collected will directly be entered into a suitable data base. |
| **Sample Size** | The prospectively calculated sample size using 2-sided *t*-test analysis aiming for a power of 95% and an alpha of 0.05 was 14 patients per group. With a drop-out rate of 15% we assumed a group size of 17 patients. |
| **Analysis and Statistics** | Continuous data will be expressed as mean ± standard deviation and compared with the unpaired student`s t-test or Mann-Whitney U test if not normally distributed. Normality will be checked with the Kolmogorov-Smirnov test. To compare multiple subgroups of normally distributed data a one-way ANOVA will be used. Statistical analysis will be performed with Prism® (GraphPad®). A p-value <0.05 will be considered to be significant. |
| **Ethics and Quality Assurance** | The study was approved by the local ethics committee. The study will be conducted according to the ICH-GCP criteria of ”Good Clinical Practice“. It will be performed according to the legal data protection requirements. The pseudonymized data will be archived for 5 years at the University Hospital Duesseldorf. Data analysis will be performed pseudonymized. Data protocol and publication will be anonymized. The patients have the right to receive information. |
| **Insurance** | No patients’ insurance is necessary because this is an observational trial. |

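### Two unranked primary endpoints, each judged at 0.05, have no success rule: an either-endpoint claim exceeds the stated alpha, and a both-endpoints claim may fall short of the stated power

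*Protocol*

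**What the plan says.** The Objectives row of the protocol asks whether guidance by the fusion imaging system lowers radiation exposure. It then states: "Primary endpoints are the change of total radiation dose and fluoroscopy time". The two measures are not ranked, and the row does not say whether one or both must be significant.

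The Sample Size row gives one calculation. It begins "The prospectively calculated sample size using 2-sided", refers to a t-test, and continues "aiming for a power of 95% and an alpha of 0.05 was 14 patients per group". It adds: "With a drop-out rate of 15% we assumed a group size of 17 patients". It gives no endpoint, effect size or standard deviation.

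Under Analysis and Statistics, continuous data are to be "compared with the unpaired student`s t-test or Mann-Whitney U test if not normally distributed", and the only decision threshold is: "A p-value <0.05 will be considered to be significant". The protocol contains no adjustment, hierarchy or co-primary rule.

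**The concern.** One claim rests on two tests, and the protocol states one alpha and one power figure for it. Two simple success rules are open, and they affect those figures differently.

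- **Either endpoint suffices.** There are two chances of a false positive at 0.05 each, so the error rate of the overall claim is above 0.05.
- **Both endpoints are required.** The error rate stays at or below 0.05, but the chance that both succeed is generally lower than the chance that one does. The 95% then need not apply to the claim.

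Without a rule, a significant fluoroscopy time with a non-significant dose could be reported as showing lower exposure, although dose is the more direct measure of the objective. The study is open-label, which makes a rule fixed in advance more useful.

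**Working it through.** **Inputs from the protocol.** Two primary endpoints (Objectives). Two-sided t-test, alpha 0.05, power 95%, 14 per group, 15% drop-out, 17 per group (Sample Size). Unpaired test and threshold 0.05 (Analysis and Statistics).

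**Assumptions, because the protocol gives no figure.** Standardised effect d, taken as equal for both endpoints unless stated otherwise. Correlation between the endpoints, shown from 0 to 0.9.

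**Step 1: the plan's own figures.** The 14 per group cannot be reproduced without an effect size. It can be inverted. With noncentral-t power, 26 degrees of freedom and noncentrality d × √(14/2), 95% power at two-sided 0.05 gives d = 1.416 (about 1.42). The drop-out step does reproduce: 14 / 0.85 = 16.5, rounded up to 17.

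**Step 2: either endpoint suffices, no true difference on either.** If independent, the error is 1 − 0.95² = 0.0975. The upper bound under any dependence is 0.05 + 0.05 = 0.10. For correlated endpoints, pairs of t-tests were simulated with 14 per group (table below). This step does not depend on d.

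**Step 3: both endpoints required, each with d = 1.416 and 14 evaluable per group.** If independent, joint power is 0.95² = 0.9025. The lower bound under any dependence is 0.95 + 0.95 − 1 = 0.90. Correlated values come from the same simulation.

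| Assumed correlation | Type I error, either suffices | Joint power, both required |
| --- | --- | --- |
| 0 | 9.75% | 90.3% |
| 0.5 | 9.1% | 91.2% |
| 0.7 | 8.4% | 91.9% |
| 0.9 | 7.1% | 93.1% |

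**Step 4: how far Step 3 depends on its assumptions.**
- *Unequal effects.* If the second effect is 1.5 times the first (d = 2.12), that endpoint alone has 99.97% power, and joint power under independence is 0.95 × 0.9997 = 0.950. The shortfall is gone.
- *All 17 per group evaluable.* At d = 1.416 each endpoint has 97.94% power, and joint power under independence is 0.9794² = 0.959, above 95%.

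**Step 5: what remedies would cost in sample size (d = 1.416).**
- *Bonferroni, 0.025 each.* Power per endpoint is 90.7% at 14 per group. To reach 95% needs 17 evaluable (95.7%; 16 gives 94.4%), and 17 / 0.85 = 20 enrolled per group.
- *Both required, independent.* 95% joint power also needs 17 evaluable (95.9%; 16 gives 94.5%), so 20 enrolled per group.
- *Fixed sequence.* The first test keeps the full 0.05, so the 14 and 17 per group are unchanged, provided the calculation was made for the endpoint tested first.

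**The case against.** Four arguments can be made for the plan.

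- **The power shortfall is not established.** This stands. It rests on a back-solved effect applied to both endpoints. A reader might infer that the plan must miss either its alpha or its power whatever rule is chosen. The documents do not support that. If both endpoints are required, alpha holds, and the power loss vanishes under a larger second effect or with 17 evaluable per group. The stated 95% is tied to 14 per group, however, and extra patients do not lower the type I error of an either-endpoint claim.
- **The study is observational, and a statistical analysis plan may deal with multiplicity.** This lowers the severity but does not remove the point. The protocol itself fixes two primary endpoints, one threshold and one alpha and power pair, and any later rule must be reconciled with them. It would also be too strong to say that the error rate is uncontrolled: it cannot exceed 10%.
- **Dose is not ranked first in the protocol.** True. Placing it first is a proposal based on the stated objective.
- **The word *change* is harmless.** A reader might infer that the primary endpoint cannot be computed, since the Visit Schedule collects periprocedural data at one visit only. The two defined groups and the unpaired test make clear that a between-group difference is meant. This is loose wording, not a failed analysis.

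**Conclusion.** The concern holds as an unstated success rule for two primary endpoints, and it should be fixed. If one significant endpoint is enough, the type I error of the claim is above the stated 0.05: 9.75% if independent, falling to about 7.1% at a correlation of 0.9. This rests only on the number of tests and the assumed correlation. If both are required, the type I error is within 0.05. Joint power at 14 evaluable per group is then about 90% to 93%, on the further assumption that each endpoint has exactly 95% power (d about 1.42). The direction of the first result is firm. The size of the second is conditional.

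**What to change.** 1. State the success rule in the protocol before the data are analysed. One workable rule is a fixed sequence: test the between-group difference in total radiation dose at two-sided 0.05, then test fluoroscopy time at 0.05 only if dose is significant. This holds the overall error at 0.05.
2. State which endpoint, effect size and standard deviation the 95% power refers to. The figure should not simply be assigned to dose, because the protocol gives nothing to support that. If both endpoints are to be required, restate power as about 90% under the equal-effect assumption, or plan 17 evaluable (20 enrolled) per group.
3. As a minor edit, replace the word *change* in the endpoint definitions with difference between groups.

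**Cost.** A few sentences, plus documentation of the sample size inputs. Under the fixed sequence, group sizes stay at 14 and 17 if the calculation was made for dose. The downside is that fluoroscopy time cannot be claimed as a primary result if dose is not significant. The protocol plans last patient out for Q4 2014 but cites a 2015 publication, so the sponsor should record when the rule was fixed. A rule chosen after the results were seen would not protect the error rate.

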**Study Flow Chart**

Table 1: Visit Schedule

| **Procedure** | **Screening/**  **Baseline Visit**  **V1** | **Procedure**  **V2** | **Follow-up Visits**  **V3** |
| --- | --- | --- | --- |
| Informed Consent | X |  |  |
| In-/Exclusion Criteria | X |  |  |
| Physical Examination | X |  | X |
| Medical History | X |  | X |
| Vital Signs | X |  | X |
| TTE | X |  |  |
| TEE | X | X |  |
| Periprocedural data (e.g. procedure time, radiation time) |  | X |  |
| Laboratory analysis* | X |  |  |
| Adverse event assessment |  | X | X |

* GFR, Creatinine, Urea, Protein, Albumin, Creatine kinase, Lactate dehydrogenase, Troponin, INR, Prothrombin time, Partial thromboplastin time, Fibrinogen, BNP, Blood count, Blood glucose.

This clinical investigation plan was subject to critical review and has been approved by the following:

